## Methods

2

### Study design

2.1

In the two-arm multicentered efficacy RCT, participants are allocated to either the IG or the CG at a 3:1 ratio by means of block randomization with varying block sizes stratified by rehabilitation center. The IG will get access to either the unguided *marena* (IG subgroup 1) or *marena* in combination with the guided *GSA-Online plus* (IG subgroup 2) based on their specific indication criteria (see Table 1). The CG will receive optimized treatment as usual with access to a survey feature within the *marena* application. A Consolidated Standards of Reporting Trials (CONSORT) flow diagram is shown in Fig. 1.

**Table 1 t0005:** Indication criteria.

Intervention	Indication criteria
IG subgroup 1	Patients … (a) in need of support in the process of transferring knowledge, skills and strategies acquired during inpatient rehabilitation into everyday life and work, or (b) in need of rehabilitation-related information regarding benefits, eligibility, legal issues and procedures, or (c) who need support and structured information on occupational reintegration (e.g., information about responsible authorities, forms, deadlines).
IG subgroup 2	Patients who additionally experience… (a) a specific need for occupational-related treatment (assessed with the social medical risk index SIBAR) or (b) subjectively high psychological stress (anxiety, feelings of being overwhelmed) related to returning to work, or (c) social stress or interpersonal conflicts at work, or (d) a high subjective need for individual therapeutic guidance in (c.1) dealing with stressful situations at work and developing personal coping resources or in (c.2) coping with recurrent unfavorable interpersonal interactions at the workplace.

**Fig. 1 f0005:**
[figure not shown]
CONSORT-EHEALTH flow chart of the study design.

### Recruitment and eligibility criteria

2.2

A total of *N* = 400 rehabilitants are planned to be included in the study. Participants with various indications will be recruited during inpatient psychosomatic, orthopedic, or cardiological treatment in four rehabilitation centers in Germany. Rehabilitation entails an intensive examination, information about the individual's disease or disability, and the definition of rehabilitation goals to be achieved through various on-site measures. Patients are taught coping strategies to help them cope with the illness or disability in everyday life after rehabilitation. Since the majority of patients in rehabilitation are currently unable to work or are at risk of reduced earning capacity, this also entails dealing with occupational problems. Medical rehabilitation typically lasts 3 weeks. Psychosomatic rehabilitation typically last five or six weeks.

All rehabilitants are screened for eligibility based on clinical routine data through the clinic staff of the rehabilitation centers. The inclusion criteria are: (1) planned return to work (full- or part-time); (2) age 18 to 65 years; (3) (undisturbed) access to a computer/mobile device and the internet; and (4) German Pension (federal or regional) or statutory health insurance as rehabilitation institution. The exclusion criteria are (1) current unemployment or reduced earning capacity pension with no immediate prospect of employment and (2) negative prognosis for employment (ability to work on the general labor market <3 h as assessed in rehabilitation). No specific diagnoses will be excluded from participation.

Eligible rehabilitants will be personally informed in a group presentation by the clinic staff or members of the study team. Furthermore, they will be provided written study information and a study flyer with a link to the study homepage. Upon receipt of the signed informed consent, clinical staff will assess whether IG subgroup 1 or IG subgroup 2 is indicated and provide the study team with the recommendation for an intervention subgroup and data needed for enrollment. Table 1 provides a listing of the indication criteria for each subgroup. Indication criteria were defined based on the *GSA-Online plus* implementation study and the clinics' assessment of the expected support needed by patients. We anticipate that one-third of eligible participants will get a referral for *GSA-Online plus*. The study team will randomly assign participants to the IG or CG and assign IG participants to the recommended subgroup. After randomization, participants will receive an e-mail with initial data to log into the allocated interventions.

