### Randomization

2.3

Participants will be randomized to either IG or CG in a 3:1 ratio, stratified by rehabilitation center. Randomization lists with permuted blocks of variable lengths will be created. Upon enrollment of participants by the clinic staff, the study team will access the respective randomization list provided by an independent researcher not otherwise involved in the study. If a participant is allocated to the CG, this is entered within *marena*. If a participant is allocated to the IG, the subgroup recommended by the clinical staff is entered within *marena.* Participants will be informed about their group assignment in the registration e-mail. Due to the nature of the interventions, blinding of the group assignment is not possible.

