#### Other assessments

2.6.3

Demographic and socioeconomic characteristics from clinical routine data include age, sex, marital status, level of education, professional qualifications and apprenticeships or studies.

Occupational data include weekly working hours, receipt or application for a pension, unemployment at the time of admission, and incapacity to work in the last 12 months before admission to rehabilitation.

Inpatient treatment data includes admission and discharge dates, discharge type, and ICD 10 diagnoses.

Recommendations for medical procedures and rehabilitation aftercare by the rehabilitation clinic are documented.

General feedback is assessed through a self-constructed item (‘What else would you like to tell us?’).

Adherence is assessed in different areas throughout *marena*. To analyze the use of the task organizer the number of completed tasks will be examined in relation to the number of tasks that became active in the participant's aftercare plan. Adherence is operationalized by the percentage of participants who completed at least the lower quartile of the provided tasks (in relation to the sample). Additionally, the number of sessions, completed weekly surveys, media playback, visits to the intervention areas, and individual pages will be analyzed. To operationalize adherence to *GSA-Online plus*, the number of completed writing-impulses will be assessed. Adherence will be operationalized by the percentage of participants who wrote at least the lower quartile of diary entries written in the sample.

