### Sample size

2.7

The sample size was determined a priori using SAS 9.4 software. A Power analysis based on a power of 0.80, two-sided testing, an alpha-rate of 5 %, and a randomization ratio of 3:1 was conducted. According to Bethge (2017), Odds Ratios of 3.49 (referring to Streibelt and Bethge, 2014) and 2.41 (in Bethge et al., 2011; overall in Streibelt and Bethge, 2014) were observed for work-related occupational rehabilitation programs versus medical rehabilitation with regard to work status 6 months after discharge from rehabilitation. We plan more conservative with an Odds Ratio of 2.0. According to Bethge (2011), a work status rate of 51 % in the CG could be assumed. These assumptions resulted in a total sample size of *N* = 360 required for 80 % power and a binary logistic regression model to analyze the primary endpoint. When considering a correlation of ρ = 0.4 with indicators of specific occupational problems (at least 3-months of incapacity to work before rehabilitation, unemployment at the time of application, and the socio-medical assessment of limited performance in the last occupational activity; see also Bethge, 2017), the sample size can be reduced by ρ2 = 16 % to *N* = 320, due to the reduction of total variance through the explained variance of the covariates. Based on an estimated dropout rate of 20 % at the follow-up assessments T1 (at the end of the *GSA-Online plus* intervention) and T2 (at the end of the *marena* intervention) we plan to randomize *N* = 400 patients.

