### Statistical analysis for primary and secondary outcomes

2.9

All data analyses will be performed after completion of data collection and on intention-to-treat basis. The significance level for all analyses will be defined as *p* = .05. If appropriate, results will be displayed by adjusted estimates from the analysis model, and their respective 95 % confidence intervals. Descriptive statistics will be used to describe demographics and baseline characteristics. To examine differences between IG and CG in the dichotomous primary outcome work status at 6 months (T2, primary endpoint) and 12 months (T4, secondary endpoint), a binary logistic regression model with fixed and random effects will be performed. In the logistic regression model the following parameters will be considered as fixed effects: treatment group (IG/CG), study site, operating system (android/iOS), at least 3-month incapacity for work before rehabilitation (yes/no), and unemployment at the time of admission to rehabilitation (yes/no). The social-medical risk index (SIBAR) as a continuous parameter will serve as a random effect. In addition, per protocol analyses will be performed to examine the impact of dropouts on study results. Dichotomous secondary outcomes will be analyzed accordingly. Continuous outcome measures will be analyzed with a covariance model for repeated measures. Compound symmetry will be assumed. Additionally, per protocol analyses (based on data of those participants who completed at least the lower quartile of tasks provided in *marena* in relation to the sample and participants who wrote at least the lower quartile of diary entries written in the *GSA-Online plus* sample) will be performed to examine the impact of dropouts on study results. Furthermore, other possible influencing factors (e.g., IG subgroup 1 and IG subgroup 2, received aftercare vs. not received aftercare) will be examined in an exploratory way. The results will also be displayed by rehabilitation center to explore whether obvious differences in effect sizes by rehabilitation center are apparent.

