Finally, we will be able to enroll a variety of patients in the target population of this study by recruiting across indications, in four different states, and in clinics with different health care providers (two German Pension insurance clinics, two private clinic operators). Participants will not be compensated for their participation. This real-world setting, reflecting the conditions of health care services, will add considerable validity to future findings and will provide very valuable information on the generalizability of study results as well as the long-term implementation and dissemination of both interventions.

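### Indication area is named neither in the primary model nor in the planned breakdown of effects: no bias, a small loss of precision at most, and no named check behind the cross-indication statement

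*Protocol article*

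**What the plan says.** Section 2.2 states the pooling: "Participants with various indications will be recruited during inpatient psychosomatic, orthopedic, or cardiological treatment in four rehabilitation centers in Germany". It also gives a longer usual stay for psychosomatic rehabilitation (five or six weeks) than for medical rehabilitation (three weeks).

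Section 2.3 gives the allocation: "Participants will be randomized to either IG or CG in a 3:1 ratio, stratified by rehabilitation center".

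Section 2.9 lists the fixed effects of the primary logistic model: "treatment group (IG/CG), study site, operating system (android/iOS), at least 3-month incapacity for work before rehabilitation (yes/no), and unemployment" at admission. The continuous social-medical risk index (SIBAR) is added as what the article calls a random effect. The one breakdown of effects to which 2.9 commits is this: "The results will also be displayed by rehabilitation center to explore whether obvious differences in effect sizes by rehabilitation center are apparent". Section 2.9 also foresees exploratory work on further influencing factors. That list is open, and its two examples are the intervention subgroup and receipt of aftercare.

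Section 2.6.3 lists ICD-10 diagnoses among the inpatient treatment data. Section 3.1 counts as a strength "recruiting across indications, in four different states, and in clinics with different health care providers" and links this to generalisability.

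**The concern.** Three patient groups with different treatment programmes are analysed together for a return-to-work endpoint. If their chances of a positive work status differ, indication area is a prognostic baseline factor. The clinics know it from the type of treatment the patient is receiving, so it is available in both arms without new data collection. It is nevertheless absent from the model list, while operating system has a term there.

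Two things are at stake. The first is precision. The step from 360 to 320 evaluable patients in section 2.7 relies on variance explained by covariates, and the indicators named there concern occupational problems, not indication. The second is interpretation. A reader of the results will ask whether the effect looks alike in psychosomatic and somatic patients, and no named analysis shows this. A display by centre cannot isolate indication, since the centres also differ in state and operator.

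**Working it through.** **Inputs from section 2.7:** "power of 0.80, two-sided testing", "an alpha-rate of 5" per cent, allocation 3:1, CG success rate 51%, odds ratio (OR) 2.0, dropout 20%, 400 randomised.

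**Assumed, because the article gives no figures:** three areas of equal size, and the CG success rate within each area.

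**1. The plan's own figure.**
- CG odds: 0.51/0.49 = 1.041. Doubled: 2.082. IG rate: 2.082/3.082 = 0.6755.
- Mean rate: (0.51 + 3 × 0.6755)/4 = 0.634.
- CG size: [1.96·√(0.634 × 0.366 × 4/3) + 0.842·√(0.51 × 0.49 + 0.6755 × 0.3245/3)]² / 0.1655² ≈ 89.8, so 90 CG patients and a total of 360. This reproduces.
- 320/0.80 = 400 also reproduces.
- The step between does not: 360 × 0.84 = 302, not 320. That errs on the safe side and does not affect this point. I use 320 evaluable patients (240 IG, 80 CG).

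**2. Chance imbalance without stratification by indication.** The SD of the IG-CG difference in one area's share is √[1/3 × 2/3 × (1/80 + 1/240)] = 0.061. The 95% range is ±1.96 × 0.061 = ±0.119, about ±12 percentage points. With all 400 it is about ±11. It is smaller where indication is nested in centre, because centre is a stratum.

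**3. Power gained by adjusting for indication.**
- Unadjusted: the variance of the log OR is 1/(0.2499 × 80) + 1/(0.2192 × 240) = 0.0690, SE 0.263. Then 0.693/0.263 − 1.96 = 0.68, power 75.1%.
- Adjusted: inverse variances are summed over the three areas, with the overall OR held at 2.0.

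| Assumed CG rates by area | Conditional OR | Power, adjusted | Gain (points) |
|---|---|---|---|
| 51/51/51% | 2.00 | 75.1% | 0 |
| 46/51/56% | 2.01 | 75.4% | 0.3 |
| 41/51/61% | 2.04 | 76.1% | 1.0 |
| 36/51/66% | 2.08 | 77.2% | 2.1 |
| 28/51/74% | 2.23 | 80.3% | 5.2 |

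These gains are upper limits, since the comparison model has no site term and the planned model has one.

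**4. The same with site in the model.** This was simulated with four sites of 60 IG and 20 CG patients, indications mixed in every site, OR 2.0 within indication, and 1,500 trials per scenario.
- CG rates 40/51/62%: power 73.1% without and 73.8% with indication, which is within Monte Carlo error (SE about 1.1 points).
- CG rates 30/51/72%: 66.4% against 70.7%.
- One indication per site: no difference.

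**5. What a display by indication could show.** Each area has 320/3 ≈ 107 patients, about 27 CG and 80 IG. The SE of the log OR is √[1/(0.2499 × 26.7) + 1/(0.2192 × 80)] = 0.455. With a true OR of 2.0, the expected 95% CI is 2.0 × exp(±1.96 × 0.455), or 0.82 to 4.88. Power is about 34%. For areas of 50 to 200 patients it is 19% to 56%.

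**The case against.** The strongest reply is that site already does this work. Site is both the stratum and a fixed effect, and the abstract speaks of medical and psychosomatic clinics, so much of the contrast may lie between centres. This stands as a limit on the size of the point. It does not remove it, because the centre-by-indication mapping is not given and three indications are spread over four clinics.

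It is also fair that the article nowhere says indication area predicts return to work. The introduction names depression, anxiety and somatic symptoms, which are scores measured in each patient. The success rates by area are therefore assumptions, and the 5-point gain needs a very wide spread. The simulation also omits SIBAR, prior incapacity and unemployment, which could absorb part of any difference.

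A reader might infer three stronger things that the document does not support:

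- **That the primary result is biased.** It is not. Chance imbalance under randomisation is covered by the confidence interval.
- **That the effect across indications will not be examined at all.** The exploratory list is open, and subgroup detail may sit in an analysis plan that is not shown. Section 3.1 claims varied enrolment in a real-world setting, not equal effects.
- **That the yes/no term for three months of incapacity throws information away**, since section 2.6.3 records "incapacity to work in the last 12 months before admission to rehabilitation". The next sentence of 2.9 brings in SIBAR as a continuous score, and section 3.2 says the screening instrument includes duration of incapacity. The form in which the 12-month history is held is not stated. No change to that indicator is justified on this evidence.

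Finally, no variable called indication area is defined, and the time at which ICD-10 diagnoses are recorded is not given. That the clinic knows the indication at enrolment is an inference, but a safe one: patients are recruited during treatment of a given type.

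**Conclusion.** The point holds in a limited form. Indication area is missing from a model list and from a breakdown that section 2.9 itself fixes, while section 3.1 draws on recruitment across indications. The article contains no error or contradiction here, and the randomised comparison stays valid.

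The size is modest. If indications are mixed within centres, adjustment is worth about 0 to 1 point of power for moderate prognostic differences and up to about 5 for large ones. If each centre treats one indication, it is worth nothing. The imbalance range of about ±12 points and the 34% power per area both rest on equal thirds and 320 evaluable patients. The more lasting gain is interpretive: a named, descriptive look at the effect by indication where none is now named.

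**What to change.** In section 2.9 and the analysis plan, before outcomes are seen:

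1. Add indication area (psychosomatic, orthopaedic, cardiologic), as known to the clinic at enrolment, as a fixed effect in the primary and secondary models. Drop it only if it is fully aliased with site.
2. Next to the display by centre, show the IG-CG effect with its 95% CI by indication area. Label it descriptive, and say that each area has low power (about 34% under equal thirds).

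Stating which indications each centre treats would show how much the new term can add.

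The cost is wording, with no new patients, procedures or data collection. The model uses up to two more degrees of freedom, and its odds ratio becomes conditional on indication as well as on the covariates already listed. The sample size does not change.

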### Randomization

2.3

Participants will be randomized to either IG or CG in a 3:1 ratio, stratified by rehabilitation center. Randomization lists with permuted blocks of variable lengths will be created. Upon enrollment of participants by the clinic staff, the study team will access the respective randomization list provided by an independent researcher not otherwise involved in the study. If a participant is allocated to the CG, this is entered within *marena*. If a participant is allocated to the IG, the subgroup recommended by the clinical staff is entered within *marena.* Participants will be informed about their group assignment in the registration e-mail. Due to the nature of the interventions, blinding of the group assignment is not possible.

### Interventions

2.4

Initial login data for the interventions is received via e-mail while still in inpatient rehabilitation. Participants will be granted access after setting an individual username and password.

#### marena

2.4.1

Participants of the IG have access to the unguided self-help intervention *marena* for a period of 6 months following discharge from rehabilitation. The content of *marena* is based on comprehensive research of respective literature. This includes research on well-established strategies in inpatient treatment, as well as information on financial and practical measures relevant to the rehabilitation process. These strategies range from audio exercises covering relaxation techniques (Deutsche Rentenversicherung Bund), emotional awareness (Martins et al., 2010; Kraiss et al., 2020), and mindful eating (Robinson et al., 2013; Warren et al., 2017) to information on the benefits of physical activity (Pedersen and Saltin, 2015), work breaks and leisure-time (Sonnentag et al., 2010; Hunter and Wu, 2016; Bennett et al., 2018; Wiese et al., 2018), and goal-setting (Schumacher; Maclean and Pound, 2000). Information on financial and practical measures relates, for example, to graded return to work (Deutsche Rentenversicherung Bund, 2023a), benefits for participation in working life (Deutsche Rentenversicherung Bund, 2018), reintegration management (Deutsche Rentenversicherung Bund, 2023c), and financial aid during sickness and rehabilitation (Deutsche Rentenversicherung Bund, 2023b; §§ 44 ff. SGB V).

Furthermore, structured interviews (*N* = 11) were conducted with experts from research and practice to determine the specific focus of the intervention. Case groups based on work-related rehabilitation goals were defined and frequent, prototypical pathways and associated obstacles were identified. Features and contents were adapted through constant feedback loops with the experts interviewed beforehand.

Consequently, the intervention consists of four main areas: (1) a task organizer where participants can create their own and receive tasks according to three different aftercare plans, (2) a strategy area with summaries and audio exercises for a collection of strategies known from rehabilitation (e.g., physical activity and relaxation techniques), (3) frequently asked questions with specific information on financial and practical measures (such as sickness benefit and graded return to work) and (4) a contact directory.

Ultimately, a prototype of *marena* was piloted with *N* = 7 rehabilitation patients. The qualitative Think Aloud method was used in semi-structured interviews with patients accessing the *marena* intervention on their private mobile devices. Participants performed different tasks based on the key features in each section of the intervention and were asked to verbalize their thoughts while performing tasks and activities. Recommendations for improvement were then made based on participants' comments about the content, appearance, or functionality of *marena*. The intervention was then updated accordingly.

A (1) return to work aftercare plan is preselected and requests participants to specify aftercare goals while still in inpatient rehabilitation. The intervention encourages participants to discuss their aftercare goals with health professionals in the rehabilitation centers. Following discharge from inpatient rehabilitation, *marena* provides weekly tasks to work on these goals and refers to other related areas of the intervention (e.g., topics such as motivation, mindfulness, or physical activity in the strategy area). Participants can additionally specify if they (2) undertake graded return to work or apply for (3) benefits for participation in working life. The graded return to work aftercare plan contains tasks with information on the procedure as well as reminders on important appointments and forms. The benefits for participation in working life aftercare plan contains tasks that guide participants through the application process with references to necessary information and application forms. Facing typical obstacles or setbacks during occupational reintegration, participants can report changes in return to work dates, sickness within graded return to work, and different responses to a benefit for participation in working life application. The intervention provides corresponding tasks with recommended actions and contacts. Activity, due date, and content of tasks are dependent on patients' profile data. Each plan provides relevant contacts.

Within *marena* participants are offered a voluntary weekly survey. This survey includes three items on health status (EQ-VAS), workload (SIBAR subscale occupational stress), and ability to work (WAS). If participants regularly complete these surveys, they can view a corresponding graph for each item in their profile over the course of program participation.

Participants receive reminders on new due tasks, study surveys, and after 14 days of inactivity. Depending on the operating system, reminders will be sent via e-mail and/or push notification. For excerpts from the *marena* intervention, see Fig. 2.

